## Abstract

**Background:**

Patients with self-harm and suicidal ideation are increasingly presenting in emergency departments (ED) in the UK. Self-harm is the strongest risk factor for suicide. Currently, there are no evidence-based interventions for self-harm offered in the context of general hospitals in the UK. This trial, funded by the National Institute for Health and Care Excellence (NIHR), aims to assess the clinical and cost-effectiveness of the ASSURED intervention. The ASSURED intervention includes up to five rapid follow-up contacts, comprising a narrative interview and enhanced safety planning session and three solution-focused sessions. The trial is sponsored by Devon Partnership NHS Trust and City St George’s, University of London.

**Methods:**

ASSURED is a multicentre, two-arm, parallel-group, individually randomised, controlled trial comparing the ASSURED intervention with usual care. The primary outcome is whether study participants re-attend ED and are referred to liaison psychiatry within 18 months from the date of randomisation. Secondary outcomes include suicidality, self-reported self-harm, psychological wellbeing, social outcomes, experiences of attending the ED, and suicide. The study will also evaluate the cost-effectiveness of the intervention. The aim of this study was to recruit and randomise 620 patients across 14 acute hospital sites in London, Devon, Somerset, and the Midlands. Participants are invited to complete research assessments at baseline and 3, 9, and 18 months. The first participant was enrolled in the study in August 2022, and the recruitment target was met in December 2024.

**Discussion:**

This will be the first UK trial to test the effectiveness and cost-effectiveness of a rapid intervention for patients presenting to EDs with self-harm and suicidal ideation and has the potential to improve outcomes for these patients.

**Trial registration:**

ISRCTN 13472559. Registered on 18 of November 2021.

**Supplementary Information:**

The online version contains supplementary material available at 10.1186/s13063-025-09411-7.

## Introduction

### Background and rationale {9a}

Death by suicide is a catastrophic loss of life for the person and the people they leave behind: children, partners, family, and friends. Self-harm and suicidal ideation are key risk factors for suicide. Self-harm refers to intentional self-poisoning or self-injury, irrespective of the apparent purpose of the act [1]. For patients, self-harm is associated with significant personal suffering, poor mental health, poor quality of life, and needs for support from carers and services [2, 3]. Each year, approximately 220,000 episodes of self-harm by 150,000 people are managed by emergency departments (EDs) in England [4]. The Government’s Suicide Prevention Strategy for England has prioritised support for people who self-harm and highlighted the role of EDs [5]. In addition to the high numbers of people presenting to EDs with self-harm, there are increasing numbers of people presenting to EDs with suicidal ideation, which is also an important risk factor for suicide [6, 7]. Both those presenting to the ED with self-harm and suicidal ideation have been identified as warranting personalised management plans and active follow-up to reduce the risk of self-harm [6, 8].

In England’s National Health Service (NHS), the National Institute for Health and Care Excellence (NICE) recommends a psychosocial assessment by specialist mental health practitioners in the ED for people who present with self-harm [9]. Most EDs have a psychiatric liaison team staffed by specialist mental health practitioners. They conduct psychosocial assessments to support patients, assess their current and future health and social care needs, and make onward referrals. While many people need further support, accessing specialised mental health services is often not a realistic option because (a) there is not enough capacity in these services, (b) specialised treatment is costly, and (c) many patients do not attend or withdraw from treatment [10]. Research has found that patients often feel stigmatised when seeking help in the ED for self-harm and suicidal ideation [11] and often feel care plans are not personalised or meaningful to them [12]. Furthermore, there are substantial gaps in care provision for these patients, who are often discharged without a new or active referral to mental health services [13].

The present study is part of a research programme called ASSURED which seeks to address this gap in care provision. The overall aim of the ASSURED study is to develop and trial a rapid and cost-effective intervention to improve outcomes for patients presenting to the ED with self-harm and/or suicidal ideation. The ASSURED intervention was developed based on international evidence [14], focus groups, and semi-structured interviews with stakeholders and ongoing input from a lived experience advisory group [11]. The intervention was designed to consist of an enhanced psychosocial assessment in the ED (comprising a narrative interview and enhanced safety plan), three solution-focused follow-up sessions over 8 weeks, a fifth optional session, and three personalised letters sent out over 9 months post-randomisation.

The intervention was tested in a feasibility study and followed by an internal pilot trial, conducted from July 2022 to March 2023 across four NHS hospitals in England with patients presenting with self-harm and/or suicide [15]. The original study was a cluster randomised controlled trial with participating practitioners allocated to ASSURED or treatment as usual (TAU) and the first intervention session taking place in the mental health psychosocial assessment in the ED. However, the Covid-19 pandemic meant ED practitioners’ workload increased significantly, and researchers had no access to ED sites to gain consent from patients before their psychosocial assessment. Hence, the pre-COVID cluster randomised controlled trial had to be modified. The key changes were moving to individual patient randomisation, patient consent soon after ED attendance, and delivering the first intervention session approximately 2 weeks after ED attendance. This removed reliance on ED and liaison staff to screen/consent patients.

### Objectives {10}

The objectives of the ASSURED trial are to (A) assess whether the intervention reduces the need for mental health reattendance at the emergency department; (B) assess whether the intervention improves secondary outcomes: mental health outcomes are suicidality (suicidal thoughts and/or plans), self-reported self-harm, psychological wellbeing, and suicide (death due to self-inflicted self-injury or self-poisoning) [16], social outcomes (accommodation, employment, partnership/family, friendships), and experiences of attending the ED; and (C) assess the costs and cost-effectiveness of the intervention.

### Patient and public involvement {11}

Patient and public involvement (PPI) has been a crucial aspect of all aspects of the study. A person with lived experience is a co-applicant on the project and part of the Programme Management Group (PMG). A Lived Experience Advisory Panel (LEAP) was set up to inform the ASSURED project, comprising a diverse group of seven people with lived experience of self-harm and/or suicidality. The group has been enthusiastic to be involved in all aspects of the project. Frequency of meetings is flexible depending on the phase of the study.

The LEAP has contributed to all aspects of the project—from designing the study logo, co-producing intervention and training materials (including a safety plan and consent forms), contributing to training practitioners, and advising on different aspects of trial procedures and dissemination. Training to participate in data analysis will be offered, with ongoing supervision and guidance from researchers during the analysis process. We will request permission from the ethics committee to consider LEAP members trained in data analysis and confidentiality as members of the research team. We would request permission for LEAP members to analyse transcripts of anonymised focus groups/interviews.

LEAP meetings are facilitated by a qualified, experienced mental health practitioner and a person with lived experience, who support a culture of open reflective communication and trust, which is modelled by the facilitators themselves. The LEAP members work together very openly, encouragingly, and cooperatively, valuing one another and making valuable contributions to the research. Open communication about any concerns or upsetting experiences or emotions is actively encouraged, with staff and facilities available to provide emotional support.

### Trial design {12}

ASSURED is a multicentre, two-arm, parallel-group, individually randomised controlled trial comparing the ASSURED intervention with usual care. Patients are randomised 1:1 in random block sizes of 4, 6, or 8 using stratification by site and type of presentation, i.e. self-harm or suicidal ideation.

## Methods: participants, interventions, and outcomes

### Study setting {13}

Recruitment for the trial takes place after patients have been seen by the liaison psychiatry teams for the standard psychosocial assessment in 14 EDs in London (Homerton University Hospital, Royal London Hospital, Newham University Hospital, Whipps Cross Hospital, University College Hospital, North Middlesex University Hospital), Surrey (East Surrey Hospital), Devon (Royal Devon and Exeter Hospital, Torbay Hospital), Somerset (Musgrove Park Hospital, Yeovil District Hospital), and the Midlands (University Hospital Coventry and Warwickshire, George Eliot Hospital, Warwick Hospital). These emergency department sites are covered by 10 different liaison psychiatry teams across East London NHS Foundation Trust, Surrey and Borders NHS Trust, Devon Partnership NHS Trust, Coventry and Warwickshire Partnership NHS Trust, North East London NHS Foundation Trust, Camden and Islington NHS Foundation Trust, Barnet, Enfield and Haringey Mental Health Trust, and Somerset NHS Foundation Trust. These hospital sites were approached based on existing annual estimates of self-harm presentations in the ED as well as the capacity and resources within the liaison psychiatry teams to undertake the study.

### Eligibility criteria: eligibility criteria for participants {14a}

#### Patient inclusion criteria

 ≥ 18 years of agePresenting to the ED and referred to the liaison psychiatry team for a psychosocial assessmentPresenting with self-harm, i.e. an intentional act of self-poisoning or self-injury, irrespective of the motivation or apparent purpose of the act *and/or* presenting with suicidal ideation, i.e. thoughts of not wanting to liveProvide informed consent to take part

#### Patient exclusion criteria

Experiencing a psychotic episodeNo capacity to provide written informed consentNeeding an interpreter, due to the additional resource requiredMinistry of Justice patients subject to a restriction orderLiving out of trust (to ensure access to medical records)Safety concerns

### Eligibility criteria: if applicable, eligibility criteria for sites and for individuals who will deliver the interventions (e.g. surgeons and physiotherapists) {14b}

The ASSURED intervention is delivered by NHS practitioners working or allied with liaison psychiatry teams (e.g. mental health practitioners, psychiatrists, doctors, support workers, psychologists, nurses, occupational therapists) as well as experienced assistant psychologists and research assistants working or affiliated (i.e. holding honorary contracts) within the participating NHS teams.

### Intervention and comparator: intervention and comparator with sufficient details to allow replication including how, when, and by whom they will be administered {15a}

Participants in the control group receive usual care. This may involve discharge to the general practitioner, referral or discharge to secondary mental health care, or psychiatric admission. Given the modified study design, it is possible that participants randomised to the control group may have received the standard psychosocial assessment by a practitioner trained in the ASSURED intervention. It is unlikely that these practitioners will deliver the additional ASSURED components (narrative interview, enhanced safety planning) due to time constraints and discharge targets in the ED. In the unlikely event that ASSURED components may be implemented in the control arm in the psychosocial assessment, any impact should be mitigated by randomisation.

Practitioners are trained in the ASSURED intervention. The ASSURED intervention manual is published online (https://assuredstudy.co.uk/manual/). In addition to usual care, the intervention involves rapid follow-up and up to five follow-up sessions over 8 weeks. Sessions are ~50 min long and are delivered flexibly depending on the person’s preference (face to face at the hospital site if a room is available, over the phone, or by video call) with (as far as possible) the same practitioner around 1 week, 2 weeks, 4 weeks, and 8 weeks after randomisation with a fifth optional bank session. These timescales are a guideline and may be used flexibly depending on the availability of the patient and practitioner.

In ASSURED, the use of language and active listening is very important. The training emphasises the importance of human connection, elaboration, validation of distress and help-seeking, and giving hope. Practitioners are trained to stay close to the person’s own words, ask open questions, and wait for people to respond and validate their difficult experiences. Practitioners are trained to use these skills in the therapeutic sessions.

In the first session, the practitioner uses narrative interview techniques to explore the person’s story [17]. The practitioner and patient then develop a personalised and enhanced safety plan [18] in the patient’s own words. The aim of the safety plan is to identify warning signs and consider steps that the person can take to manage distressing experiences such as having suicidal thoughts. These are described under “Distractions” (what can I do to distract myself?), “Changing my Environment” (where can I go to distract myself from thoughts?), “People I trust” (“Who can I contact when I feel overwhelmed?”), and “Professionals” (“Which professionals can I contact?”). The session is supported by a template that participants and practitioners complete together either online or on paper.

The patient is then offered three further solution-focused sessions [19] to explore the patient’s future hopes, along with resources and strengths already present in achieving or working towards their future hopes. The participant is asked on a scale from 0 to 10 where they are in terms of their best hopes (“If 10 is your best hopes are realised, and 0 is the opposite, where are you now on the scale?”) and how confident they feel that they can achieve their best hopes (“If 10 is – you are as confident as you can be in making progress towards your best hopes – and 0 is the opposite, where is your confidence now on the scale?”). A list of signposting resources has also been developed as part of the ASSURED intervention, and practitioners are encouraged to discuss further support with participants and, where relevant, spend 5 min at the beginning of every session checking in on any referrals made to other services. Within the ethos of the solution-focused approach, if a person misses a session, this is not perceived as nonengagement or patient “resistance”. Practitioners record the missed session, attempt to contact the patient, and reschedule the session as flexibly as possible.

The optional bank session can occur up to 9 months post-randomisation, following the solution-focused approach. The patient receives three personalised letters from the practitioner ending at 9 months to let the patient know that the practitioner is thinking of them and to remind them of the safety plan, bank session, and support networks.

### Intervention and comparator: criteria for discontinuing or modifying allocated intervention/comparator for a trial participant {15b}

There may be instances where a clinical decision is made for the patient to discontinue their involvement in the study, e.g. services may deem it likely that new mental health practitioners being introduced to a participant’s existing care could be destabilising. It is expected that this will disproportionately affect intervention participants given that there will be more contacts with the study clinicians compared to control participants. If a practitioner or a researcher deems that the patient’s risks have escalated during their participation in the study, then this will be raised immediately with the local principal investigator (PI). A decision will be made as to whether it is appropriate for the patient to continue with the intervention and research assessments. Patients enrolled in the study will still be followed up for the primary outcome (ED reattendance with referral to liaison psychiatry) unless they explicitly request that researchers do not extract their data from the medical records.

### Intervention and comparator: strategies to improve adherence to intervention/comparator protocols, if applicable, and any procedures for monitoring adherence {15c}

To improve patient adherence to the intervention, practitioners will aim for flexibility in the time and delivery of sessions. Attendance at sessions will be monitored using a form completed by practitioners. Practitioners receive 2 days of training in the intervention, conduct role-plays with trainers, and attend regular supervision. The training takes place online, usually in groups with other participating practitioners, and it is facilitated by an experienced study researcher (chief investigator, trial manager, senior research assistant). Two drop-in, peer-supervised sessions are offered every week. To mitigate against contamination, participating practitioners are reminded of the importance of not sharing details of the ASSURED intervention with other colleagues.

In addition, study researchers routinely collect data on the training and supervision that practitioners receive, i.e. date of training/supervision, length of training/supervision (mins), type of training (core, top-up, one-off), mode of training/supervision (face to face, videocall with facilitation, telephone, email, website self-learning, and other), and travel required. Data is routinely collected for all study participants in the intervention arm on intervention sessions, i.e. practitioner delivering the intervention, number of intervention sessions delivered, date of intervention session, mode (face to face, video call, telephone call), and length (mins). Fidelity to the intervention will be assessed via video and audio recordings of the intervention session where participants have provided informed consent.

### Intervention and comparator: concomitant care that is permitted or prohibited during the trial {15d}

Trial participants are permitted to receive any concomitant care during the trial.

### Outcomes {16}

The primary outcome is a binary outcome [yes (y = 1) or not (y = 0)], i.e. whether study participants re-attend ED and are referred to liaison psychiatry within 18 months from the date of randomisation. Re-attendance with referral to liaison psychiatry is any (a) attendance for self-harm or other mental health crisis, (b) a referral is made and accepted by the liaison team, and (c) the attendance and referral happen in the same ED visit. This data (i.e. date and time of referral to liaison psychiatry after ED attendance) will be obtained from NHS business intelligence teams and may be supplemented/cross-referenced with NHS England. A pre-specified data extraction protocol has been agreed upon with the NHS Business intelligence teams.

The advantage in using this method of data extraction is that the data will be available for almost all participating patients and independent of rater bias. This outcome is linked to Objective A (see the “Objectives{10}” section) and reflects the severity and impact of repeat self-harm and is widely available from routine service data. The extraction of the primary outcome data through the NHS business intelligence teams was partially piloted in the internal pilot phase of the trial [15] and is being validated across participating sites to ensure reliability in the data extraction process.

In addition to the secondary outcomes described below, during the baseline assessment, we collect sociodemographic information for participants on gender, country of birth, ethnic group, physical health conditions, psychiatric diagnosis, previous contact with mental health services, psychiatric hospital admissions, level of education, marital status, type of accommodation, living situation, dependents, employment status, receipt of state benefits, treatment history (including contact with healthcare professionals and general practitioners for self-harm and contact with mental health services), asylum-seeker status, and drug- and alcohol-related problems.

The following secondary outcomes will be assessed:Total number of patient attendances to the emergency department over 18 months following randomisation, extracted from NHS England. This outcome is linked to Objective C (see the “Objectives {10}” section).Self-reported self-harm, using text messages at approximately 1, 2, 3, 9, and 18 months. Participants who have consented to this option are approached via text messages and invited to answer the following questions: “Have you self-harmed in the past month?” (yes/no) and “How many times?” (numerical response). This outcome is linked to Objective B (see the “Objectives {10}” section).
Suicidal ideation, using the Beck Scale for Suicide Ideation (BSSI) [20] at 3, 9, and 18 months [20, 21]. This is a 21-item scale evaluating the presence and intensity of suicidal intent in the week before the evaluation. This scale shows good concurrent validity and reliability, with a Cronbach’s alpha value of *α* > 0.90. This outcome is linked to Objective B (see the “Objectives {10}” section).Use of primary and community care, medications, social services, productivity loss, and family costs will be collected using the Client Service Receipt Inventory (CSRI), administered at baseline, 3, 9, and 18 months. These outcomes are linked to Objective C (see the “Objectives {10}” section).Psychological distress measured with the Clinical Outcomes in Routine Evaluation-Outcome Measure (CORE-OM) [22, 23] at 3, 9, and 18 months. Coefficient *α* for all domains is > 0.75 and < 0.95 [24]. This outcome is linked to Objective B (see the “Objectives {10}” section), and CORE-OM was selected to capture global distress beyond suicidality.Quality of life measured with EuroQol-5 Dimension-5 Level tool (EQ-5D-5L) [25] at 3, 9, and 18 months. This tool shows established test–retest reliability and convergent validity [23, 24]; in a systematic review of the EQ-5D-5L psychometric properties, eight studies have reported excellent scale agreement (*ICC* > 0.075). A great number of papers have reported strong, along with expected, correlations with other measures of health; the strongest correlations have been observed for multi-attribute utility instruments (*pooled rho* = 0.756), physical/functional measures (*pooled rho* = 0.582), and pain/discomfort measures (*pooled rho* = 0.595). This outcome is linked to Objective B (see the “Objectives {10}” section).Social outcomes, measured with the Social Outcomes Index (SIX) [26] at 3, 9, and 18 months. This 4-item tool measures social outcomes in four domains: employment (none, 0; voluntary/protected/sheltered work, 1; regular employment, 2), accommodation (homeless or 24 h supervised, 0; sheltered or supported accommodation, 1; independent accommodation, 2), partnership/family (living alone, 0; living with a partner or family, 1), and friendship (not meeting a friend within the last week, 0; meeting at least one friend in the last week, 1). The resulting score of SIX ranges from 0 to 6. SIX was selected to capture the person’s social situation (accommodation, employment, family/partnership, friendships), which can be affected by a mental health crisis. This outcome is linked to Objective B (see the “Objectives {10}” section).Psychological wellbeing—Short Warwick–Edinburgh Mental Wellbeing Scales (SWEMWBS) at 3, 9, and 18 months [27]. This is a 7-item scale measuring feeling and functioning changes. SWEMWBS captures positive aspects of mental health, such as optimism, relaxation, and social connectedness, which may be increased by solution-focused approaches. Cronbach’s alpha of > 0.70 indicates acceptable internal reliability [28]. This outcome is linked to Objective B (see the “Objectives {10}” section).Experiences of care in Accident and Emergency Questionnaire, devised for this study at the baseline research assessment soon after ED attendance. This outcome is linked to Objective B (see the “Objectives {10}” section).Death by suicide, i.e. the cause of death is intentional self-harm or undetermined intent derived from NHS/local authority/coroner records at 18 months. This outcome is linked to Objective B (see the “Objectives {10}” section).All-cause mortality at 18 months after randomisation, extracted from NHS England Data. This outcome is linked to Objective B (see the “Objectives {10}”section).

The mediator for the primary outcome is the therapeutic relationship, which is self-rated by patients on the Helping Alliance Scale [29], which has been adapted for the ED context. This scale is completed at 3 months and by the participants in the intervention group only.
The mediator for the primary outcome is the therapeutic relationship, which is self-rated by patients on the Helping Alliance Scale [29], which has been adapted for the ED context. This scale is completed at 3 months and by the participants in the intervention group only.

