#### Blinding {24 a, b, and c}

The statisticians and health economists analysing the trial data will remain blind to patient allocation until the Statistical Analysis Plan and Health Economics Analysis Plan have been signed off and the trial database finalised and locked for analysis. The researcher who recruits each patient will be unblinded to the patient’s allocation at the point of randomisation (which is after the baseline assessment). We do not anticipate blinding being an issue for the primary outcome as ED reattendances will be extracted from medical records. Similarly, this should not be an issue for the secondary outcome measures, as the majority are based on direct patient self-report. Participants are not blinded.

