## Data collection, management, and analysis

### Data collection methods: plans for assessment and collection of outcomes {25a}

All potentially eligible patients were approached for consent to join the study after ED attendance. The baseline research assessment took place after consent and prior to randomisation. Participants will be asked to complete further assessments at 3-, 9-, and 18-month post-randomisation. A subsample of approximately 30 patients, up to 30 practitioners, approximately 10 carers or trusted others (if available), and up to 10 team managers and local PIs such as liaison psychiatry team managers will be approached for a qualitative interview to explore experiences of receiving/delivering the intervention. Further details about the interviews are presented under section “Process evaluation—qualitative interviews”.

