### Statistical methods: methods for additional analyses (e.g. subgroup analyses) {27d}

In October 2022, the randomisation model was changed from clinician to individual patient randomisation, with the approval of the PSC. A total of 46 patients were recruited under the original study design. As of December 2024, the study achieved its target sample size.

While the components of the intervention have not changed, the timing of delivering the components has changed. In the original study design, the narrative interview and enhanced safety planning components were delivered in the ED, alongside the standard psychosocial assessment. Three solution-focused sessions were then delivered over a period of 8 weeks, and an additional bank session is available up to 9 months after randomisation. Seventeen out of 46 patients recruited under the original study design received the intervention in this form. When individual patient randomisation was implemented, all study participants received the standard psychosocial assessment in the ED, and intervention participants received their first session soon after (rather than in) the ED. All participants in the intervention arm (before and after the study redesign) received the same intervention sessions (one narrative interview and enhanced safety planning session and three solution-focused sessions plus an additional bank session). As such, all participants recruited under both designs will be included in the primary analysis.

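### Experience of ED care is a secondary outcome under Objective B but is measured only before randomisation, so for about 93% of participants it cannot respond to allocation

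*Protocol article*

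**What the plan says.** Objectives {10} sets Objective B as to "assess whether the intervention improves secondary outcomes", and the outcomes it names include "social outcomes (accommodation, employment, partnership/family, friendships), and experiences of attending the ED". The abstract also names ED experience as a secondary outcome.

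Outcomes {16} opens its list with "The following secondary outcomes will be assessed". One of the eleven entries is the "Experiences of care in Accident and Emergency Questionnaire, devised for this study at the baseline research assessment soon after ED attendance", linked to Objective B. The same section introduces the baseline sociodemographic data as separate from the secondary outcomes, so the questionnaire is presented as an outcome and not as a baseline descriptor.

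On timing, Data collection methods {25a} states: "The baseline research assessment took place after consent and prior to randomisation". Blinding {24 a, b, and c} gives the same order. Table 1 shows the questionnaire only in the baseline row, under pre-randomisation.

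On delivery, section {27d} says that once individual randomisation was in place, every participant had the standard psychosocial assessment in the ED and "intervention participants received their first session soon after (rather than in) the ED". It adds that 46 patients were recruited under the original clinician-randomised design, that 17 of them received the intervention with its first components in the ED, and that both groups enter the primary analysis.

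On analysis, Statistical methods {27a and b} sends secondary outcomes to a mixed model like that for the primary outcome, chosen by type of outcome, and leaves the detail to the SAP.

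**The concern.** A treatment effect can be estimated only on something that allocation is able to change. Here, for most participants, both the measurement and the care being rated come before allocation. The protocol nevertheless gives the measure to an objective worded as improvement by the intervention, under a general analysis sentence with no exemption for it.

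If an arm comparison is run and reported as an outcome, a significant difference could be read as benefit or harm, and a null result as evidence that the intervention does not change how people experience ED care. For the individually randomised patients neither reading would be justified. As written, that part of Objective B cannot be answered.

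**Working it through.** The protocol states no figure for this outcome, so there is none to reproduce. The check concerns the order of events and then how many participants it applies to.

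**Order of events, individually randomised patients**

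1. ED visit and standard psychosocial assessment (section {27d}).
2. Consent, within about two weeks of the visit (Consent {32a}).
3. Baseline assessment, including the ED-experience questionnaire (Outcomes {16}, Table 1).
4. Randomisation (sections {24} and {25a}).
5. First intervention session (section {27d}).

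The experience (step 1) and its measurement (step 3) both precede step 4.

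**Repeat measurement.** Table 1 repeats the CORE-OM, BSSI, CSRI, SIX, SWEMWBS and EQ-5D-5L at 3, 9 and 18 months. The ED-experience questionnaire is in none of those rows.

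**How many participants.** Inputs: target 620 (310 per arm), from Sample size {19}; 46 original-design patients and 17 with in-ED delivery, from section {27d}. The article says the target was met but gives no exact final total, so 620 is taken as the total and the 46 as included in it.

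- Individually randomised: 620 − 46 = 574; 574/620 = 92.6%.
- If the 46 were additional to the 620: 620/666 = 93.1%. The conclusion does not change.
- Original design: 46/620 = 7.4%.
- First components in the ED: 17/620 = 2.7%, or 17/310 = 5.5% of one arm.

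**Can the 46 answer the objective?** Assume the other 29 serve as the comparison group; the article does not give their allocation. With a two-sided 5% test and 80% power, ignoring clustering by clinician, the detectable standardised difference is

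(1.96 + 0.84) × √(1/17 + 1/29) = 2.80 × 0.305 ≈ 0.86.

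Clustering would make it larger.

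**Can a pooled comparison answer it?** If the 17 are all in the intervention arm and allocation has no effect elsewhere, a true difference of 0.86 in those 17 contributes about 0.055 × 0.86 ≈ 0.047 to the overall arm difference. With 310 per arm and complete data, the detectable difference is 2.80 × √(2/310) ≈ 0.225, nearly five times as large. A pooled comparison would be dominated by chance.

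**The case against.** The timing is not open to dispute: the sections agree with one another. The case on the other side concerns how far the conclusion goes, and several parts of it stand.

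- *No treatment effect can ever show.* A reader might infer this, but it is too absolute. The 46 early patients were randomised through their clinicians, and 17 had the first components in the ED, so their questionnaire may have followed exposure. A pooled contrast mixes a large part in which allocation has no effect with a small, clustered part in which it might.
- *Only those 46 could have met any ASSURED component in the ED.* The documents do not support this. Section {15a} allows, as unlikely, that a trained practitioner might use components in the standard assessment. Under individual randomisation that would precede allocation and should balance across arms, so it does not rescue the outcome.
- *The plan commits to a false-positive test.* No 5% test of this questionnaire is specified. The general sentence in {27a and b} covers it without exemption, but the SAP is not shown and may report it descriptively. The harm depends on an arm comparison being made and interpreted. The mismatch between objective and measurement time is in the protocol article itself, and no choice of model in the SAP removes it.
- *The item is a remnant of the cluster design.* This is plausible, since the first session then took place in the ED, but no section says why it was kept.

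One could also argue that the intervention might change how participants experience later ED visits. That is possible, but no measurement of it is scheduled.

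**Conclusion.** The point holds in limited form. ED experience is assigned to Objective B, yet it is measured only before randomisation and describes care completed before allocation. For about 92.6% of participants (93.1% if the 46 are additional to the target) a difference between arms would be chance by design. The remaining 46, with 17 exposed in the ED, would need a standardised difference of about 0.86 or more and cannot carry the objective.

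This rests on the article showing the full measurement schedule for the questionnaire, on a total close to 620, and, for the 0.86, on a 17 v 29 comparison without clustering.

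The matter should be corrected, but it is not critical. A reader might take it as a threat to the trial's main result. It is one of eleven listed secondary outcomes, and the primary outcome, sample size, safety monitoring and economic evaluation do not depend on it.

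**What to change.** Before database lock and unblinding, issue a dated change, with its reason, that reclassifies the questionnaire as a baseline descriptor with no between-arm treatment-effect test. Amend Objective B, the abstract and the secondary outcome list to match. A documented reclassification is more transparent than silent removal now that recruitment has closed.

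Report the 46 original-design patients separately and descriptively. Do not use the questionnaire as an adjustment covariate in any analysis that includes them: for the 17 exposed in the ED it may follow exposure, and adjusting for it could bias the estimate.

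If the full protocol contains a post-randomisation measurement of ED experience, state it and reconcile Objectives {10}, Outcomes {16} and Table 1 instead.

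The cost is one listed secondary outcome fewer and an amendment, which under Protocol amendments {31} goes to the Research Ethics Committee and the Health Research Authority. No new data are needed. Follow-up is scheduled to run to summer 2026 and the SAP is to be signed off before lock, so the change can be made while the analysts are still blind.
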